## 3. Discussion

So far, nutrition education about CD and diet has been focused on people suffering from CD [43,44,45,46,47] as it is necessary to improve their health and quality of life. Nevertheless, nutrition education should go beyond the patient, since family members and social environments also have an influence on the management of the disease, as previous studies have shown [48,49,50,51,52,53,54,55].

Moreover, as people with CD reported, one of the issues affecting their quality of life is their social activity [56]. These people as well as people in charge of them suffer anxiety and depression, partly due to negative feelings of bothering other people and being excluded from social activities [13,57]. Adolescents with CD describe difficulties in having confidence in other people because those people often do not know, do not understand or do not care enough about their dietary needs [58]. This likely happens because of a lack of awareness, which leads to a lack of empathy in people surrounding them. Therefore, it is very interesting to consider this aspect in the education of the general population, linked to the healthy diet learning process. 

The nutrition education programs carried out so far in schools have been mostly focused on improving the general diet and do not consider the overall situation of a non-insignificant part of the population, such as people going on a GFD. The Zeliakide program will be developed in schools because it is a trusted place for children and is where they spend most of their time [59,60]. It is their usual learning environment and is considered a suitable place for this kind of intervention [25,26,27,28,29,30,31,61,62]. 

Regarding the methodology of the program, the inquiry-based learning methodology has been chosen, where children learn by doing [32]. This methodology is well known and proven to be effective and encourages interaction and reflection among the children [63,64,65]. Many nutrition education programs focus on social cognitive theory [66,67,68,69]. However, in this case, the program goes further by adapting a methodology focused on teaching science, as one of the main goals of the curriculum of primary children is get closer to STEAM education. Moreover, the Zeliakide programme will be implemented by the Gluten3S research team, and scientists will go to the schools to explain, first hand, how to make the proposed experiments and interact with the children in the development of scientific reasoning. 

On the other hand, there is increasing concern among policy-makers and practitioners about the under-representation of girls and women in STEAM education [70]. Indeed, Kim et al. conducted a study that demonstrated how perceptions regarding the inclusion or exclusion of individuals in STEAM fields can be altered through intervention and educational initiatives [71]. In the present protocol, a female scientist will implement the programme and work in situ with children in the classroom. 

Competences and learning outcomes were carefully established prior to the design of the programme according to Bloom’s taxonomy, based on the level of cognitive abstraction [39,40]. The higher the level, the more complex the learning becomes. Subsequently, the activities were designed based on the IBL methodology, and the evaluation method for each learning outcome was defined. The wording of each question was carefully selected, with the help of the teachers involved in the project, to fit the cognitive level of children. In addition, the activities were designed to drive a measurable change in attitude towards a healthy diet in general and towards people with CD in particular. This careful procedure allows the intended objectives and measure outcomes to be effectively achieved with robustness. Therefore, the results obtained from the application of this protocol will accurately assess the changes in the knowledge and attitude of the participants. In addition, it is expected to indicate which aspects of those studied in the programme should be further developed in schools.

The design of the study also took into account the results obtained in a previous pilot work conducted by the Gluten3S research team [40,65]. This procedure is fundamental to accurately estimate the required sample size and avoid involving an excessive or insufficient number of participants, ensuring that the intervention’s effect can be properly observed. Thus, it has been estimated that a total of 144 children should be included in the study in order to detect a small-to-medium increase in knowledge, such as an increase in approximately one point on a scale of 0–4; thus, a sample size of this magnitude is necessary. 

The teaching unit is a complete set of materials, such as a student’s and a teacher’s notebook with all the activities explained in detail and various games, especially designed for the Zeliakide Programme. It also includes an innovative augmented reality application to reinforce the use of IBL methodology. It is considered that this material may be useful for future interventions or didactic activities, and it will be freely available and accessible to anyone who wants to use it, upon request. Moreover, it can be easily used autonomously by teachers and trainers. 

Zeliakide does not forget the importance of family participation in nutritional education activities, since results of a meta-analysis revealed that interventions that included family members produced larger effects than interventions focusing only on children [61,72,73,74]. Therefore, the intervention presented here includes activities to be carried out at home to involve children’s parents and guardians. Besides that, two short sessions (60 min) per week will be held at school over a period of one month. It must be highlighted that it seems to be appropriate to transmit the information in small doses and spread out over time for optimal learning [29,72,75,76,77].

The next step will be to implement and measure the effectiveness of the intervention proposed here. This step will be taken in the near future. It is important to highlight that the effectiveness of the intervention will be assessed by monitoring the participants using a questionnaire one month later. This approach takes into consideration the findings of previous studies that emphasise the significance of evaluating the long-term results. It is crucial to ensure that the acquired knowledge and behaviour can be sustained over time, thus providing a more comprehensive understanding of the intervention’s impact [77,78,79].

In this sense, it should be noted that this study has some weaknesses. It is a non-randomised trial; thus, some bias is expected. In addition, the control group attends a higher level at the same school than the intervention group, so there could be differences in knowledge and attitudes due to age. However, it has been considered that the control group would be even more different by choosing control groups of the same age but from different schools, since socio-cultural differences by territory (and consequently, by school) are an important aspect to take into account. At the same time, this weakness could be considered a kind of strength, because most interventions at schools do not consider any control group at all [80]. It is also remarkable that the design of Zeliakide is practical and suited to the reality of schools, and so it is easily applicable to other centres in the future. 

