## 2. Materials and Methods

### 2.1. Description

The Zeliakide project (the name comes from the union of two Basque words: “zeliako”, which means “celiac”, and “kide”, which means “companion”) is a one-month (4 weeks) intervention program, two-armed cluster, non-randomised and controlled trial, conducted among 10–12-year-old children with a pre- and post-intervention evaluation and 1 month follow-up to assess the effectiveness of the program.

The trial consists of a nutrition education intervention, focused on CD and the GFD. It is an intervention based on competencies and their respective learning outcomes. The teaching methodology chosen is inquiry-based learning (IBL). IBL enables children to acquire skills and knowledge through inquiry. It is a STEAM methodology that seeks to get children to ask questions, inspect, make measurements, design experiments, make logical reasoning based on evidence, and communicate the results.

The intervention is carried out by research experts in nutrition and CD, from the GLUTEN3S research team, and with experience in nutritional education activities. In addition, in order to highlight the role of women in science, they will be mainly women from this group who will go to the classroom to develop the intervention.

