### 2.2. Participants

Healthy children in the fifth and sixth years (last cycle) of primary school (10–12 years old) will participate in the study. At this age, they actively work on the concepts of diet and nutrients in the school curriculum. In addition, they also start to work on scientific competence, so it is considered the most suitable time to carry out the intervention. 

Inclusion criteria to participate in the study will be that children study in a primary school that must be used to project based learning and show interest in participating in the project. In addition, schools must have at least one class in the 5th and 6th grades of primary school. The exclusion criterion is school students who have a family or close relationship with any of the GLUTEN3S team researchers.

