### 2.4. Allocation to Groups

The distribution of the groups will be based on convenience as judged by experts (see the study flow in Figure 1). The intervention group will be made up of children whose teachers have communicated their wish to actively participate in the program. Teachers need to be involved in the intervention as they are aware of the situation in each classroom and it is necessary to carry out the activities correctly inside and outside the classroom.

As stated, the participants in the study will be students in the last cycle of primary education (10–12 years). The intervention will be carried out with pupils in the first year of this cycle (10–11 years) as, at this point, they acquire knowledge about nutrition and begin to develop scientific competence. All pupils in the same school, academic year and group should be part of the intervention group, since, from an ethical point of view, all groups should acquire the same knowledge during the school year. The control group will be formed by the students in the second year of the last cycle of the same primary school (11–12 years). 

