#### 2.5.2. Study Procedure

The study is schematically depicted in Figure 2. Data will be collected from participants before and after the intervention, using a specific questionnaire designed in order to evaluate the program (Appendix A Table A1). Due to the young age of the children, some limitations when reading and answering a questionnaire are expected, and so they will complete it in parts, thus avoiding the possible discomfort that a long questionnaire may generate in them. The pre-questionnaire part of each session will be completed at the beginning of the corresponding session and the post-questionnaire at the end of this session. They will have to complete a third questionnaire one month after the intervention in order to assess the maintenance of the acquired knowledge and behaviour. 

The pre- and post-intervention questionnaires will be completed with the help of 2–3 members of the research group, in addition to the school responsible teacher. They will help them to understand the questions they have to answer, always avoiding any influence. One month after the intervention, the post-questionnaire will be completed again with the help of the schoolteachers.

The control group will consist of a similar number of students to the intervention group; they will be part of the same school and their socio-demographic characteristics will be similar, even if they will be in the final year of the cycle. They will continue with the normal school curriculum. Students in the control group will be asked to complete a questionnaire as the intervention group, and they will have to answer it in the same month in which the intervention of the other group is being carried out. They will be helped by their teachers to understand the questions if necessary and will have to complete it in one session, since the aim is to avoid altering the usual routine of their classes.

Upon completion of the intervention, parents or guardians will be requested to fill out an online questionnaire to gather their feedback on the project as well as their children’s opinions, as reported by the parents.

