### 2.8. Statistical Analysis

The description of the characteristics of the participants and data from the pre-, post- and retention test (one month after) questionnaires will be reported per group (control and intervention). 

For the analysis of the differences between groups, a variety of statistical tests will be used depending on the type of response to the questions (continuous, discrete or qualitative). Based on the distribution of the variables of interest in the sample, descriptive statistics for continuous data will be presented using the mean and standard deviation or the median and interquartile range. Qualitative data shall be presented as frequencies and percentages. Quantitative variables will be analysed using an ANOVA of repeated measures test using the group as a factor of the independent level (parametric) or Wilcoxon’s test segmenting by group (non-parametric). On the other hand, qualitative variables in two categories will be analysed with Chi-square and Cochran’s Q tests. Finally, qualitative variables in more than two categories will be analysed with Chi-square and McNemar Bowker’s tests.

Data will be entered and analysed using SPSS 28.0 software. A confidence interval of 95% and significance level of *p* < 0.05 will be assumed.

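### Controls come from the same school because schools differ, but the stated analysis has no school term, so the within-school pairing goes unused

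*Protocol article*

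**What the plan says.** Section 2.1 describes a "two-armed cluster, non-randomised and controlled trial, conducted among 10–12-year-old children". Section 2.4 sets the source of controls: "The control group will be formed by the students in the second year of the last cycle of the same primary school". The Discussion gives the reason. Same-age controls from other schools were judged a worse match, because "socio-cultural differences by territory (and consequently, by school) are an important aspect to take into account".

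Four passages bear on how many children each school gives to each arm:
- Section 2.2, on eligibility, uses the plural: "schools must have at least one class in the 5th and 6th grades of primary school".
- Section 2.4 makes entry depend on teachers: "The intervention group will be made up of children whose teachers have communicated their wish to actively participate in the program".
- Section 2.4 also has an intake rule: "All pupils in the same school, academic year and group should be part of the intervention group".
- Section 2.5.2 promises rough balance: "The control group will consist of a similar number of students to the intervention group". The same sentence goes on to say that both arms belong to the same school.

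The number of schools is not given.

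Section 2.8 names the tests. Quantitative outcomes get a repeated-measures ANOVA "using the group as a factor of the independent level", or a Wilcoxon test split by group. Categorical outcomes get Chi-square, with Cochran's Q or McNemar-Bowker for the repeated measurements. No school factor or stratum is named.

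**The concern.** The trial is not randomised, and the same-school control is its main protection against confounding by school. The design pays for that protection with a one-year age gap between arms. An analysis that pools schools uses the protection fully only when every school contributes the two arms in the same ratio. Otherwise, part of the difference between schools is counted as a difference between arms.

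The categorical items are the more exposed. Much of the questionnaire in Table A1 is yes/no, multiple-choice or open. For such items Chi-square is the only between-arm test named, and as written it is adjusted for neither school nor baseline.

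This is separate from the question of whether children in one class are independent. That affects standard errors; this affects the estimate itself.

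**Working it through.** **Inputs from the article.** Planned total 144, which is 120 × 1.2 (section 2.3). Arms of similar size (section 2.5.2), so about 144 / 2 = 72 each. Planned effect d = 0.32 (section 2.3), used here only as a yardstick. Three measurement times. The article gives no figure for the effect of school, so there is none to reproduce.

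**Assumptions, not in the article.** Two schools, the arm sizes per school, and the gap between schools.

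**Formula.** Bias of the pooled arm difference = Σ over schools of (school's share of the intervention arm − its share of the control arm) × school mean. With two schools this is (difference in arm shares) × (school gap). It is zero with one school, and zero whenever the ratio is constant. For example, 40, 20 and 10 intervention children against 20, 10 and 5 controls give equal shares in every school.

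**Two schools, 72 per arm, gap 0.3 SD.**

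| Intervention:control, school A / school B | Difference in shares | Bias | As share of 0.32 |
|---|---|---|---|
| 36:36 / 36:36 | 0 | 0 | 0% |
| 38:34 / 34:38 | 4/72 = 0.056 | 0.3 × 4/72 = 0.017 SD | 5% |
| 50:22 / 22:50 | 28/72 = 0.389 | 0.3 × 28/72 = 0.117 SD | 36% |

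For a yes/no item answered correctly by 60% in one school and 40% in the other, the same splits give 0, 0.20 × 4/72 = 1.1 and 0.20 × 28/72 = 7.8 percentage points.

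**Other school gaps, two schools, 60 per arm.**

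| Intervention / control children by school | Gap 0.2 SD | Gap 0.5 SD | Gap 0.8 SD |
|---|---|---|---|
| 32+28 / 28+32 | 0.013 | 0.033 | 0.053 |
| 35+25 / 25+35 | 0.033 | 0.083 | 0.133 |
| 40+20 / 20+40 | 0.067 | 0.167 | 0.267 |

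**Which tests are affected.** If a school's level is the same at every time, it subtracts out of each child's change. It therefore drops out of the group-by-time test but stays in a single-time-point comparison and in the ANOVA group main effect. A simulation of 4,000 trials checked this, with total SD 1 at each time, within-child correlation 0.5, and the 40+20 / 20+40 split:
- Level gap 0.5 SD, no gap in change: post-test bias 0.176 without a school term and 0.009 with it (formula: 0.167 without). Change-score bias 0.003 even without a school term.
- Level gap 0.5 SD plus a 0.3 SD gap in change: change-score bias 0.096 without a school term and −0.005 with it (formula: 0.3 × 20/60 = 0.100 without).
- The second scenario at the milder 35+25 / 25+35 split: change-score bias 0.049 without a school term and −0.002 with it.

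**The case against.** The case for leaving section 2.8 alone has five parts.

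**Balance may hold per school.** A reader might infer that similar numbers are promised only across the whole trial. The sentence in section 2.5.2 does not say so. It joins similar numbers and same school, and a per-school reading is at least as natural. The fair statement is that the text does not specify.

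**Large imbalance is unlikely.** A reader might infer from the reliance on willing teachers that the number of year 5 classes could vary freely within a school. The intake rule in section 2.4 points the other way: a school's year 5 pupils enter together, so what remains is mainly the ordinary difference in enrolment between adjacent years. A 50:22 and 22:50 split would need year 5 to be more than twice year 6 in one school and the reverse in the other.

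**There may be one school.** Sections 2.4 and 2.5.2 use the singular, and the plural in section 2.2 is part of an eligibility rule. With one school the bias is exactly zero.

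**The primary outcomes are changes.** Table 3 defines them so, and stable school levels cancel in the group-by-time test.

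**This is an article.** A covariate or stratum might be left to a fuller analysis plan.

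The first four stand as limits on the size and reach of the bias. The last stands only in part. Section 2.8 is not silent on the model: it names its between-child factor, and what it names leaves out the variable on which the Discussion defends the design.

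**Conclusion.** The design and the stated analysis do not match: schools are treated as important when controls are chosen and are absent when arms are compared. That holds on the text alone.

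Bias follows only if several schools take part and their intervention-to-control ratios differ. Under the assumed two schools and 0.3 SD gap it runs from 0 through 0.017 SD for a small enrolment difference to 0.117 SD in a deliberately extreme split. Larger gaps scale it in proportion.

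A reader might infer that the planned analysis is biased by about a third of the planned effect. The article does not support that: the figure needs the extreme split. In the group-by-time test it would also need schools to differ by 0.3 SD in change over the study, which nothing in the text suggests. Level differences matter only for the single-time-point Chi-square tests and the ANOVA group main effect.

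The change is still worth making, since it is cheap and uses a protection the design has already paid for.

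**What to change.** Add to section 2.8 that, if more than one school takes part, all between-arm comparisons are made within school:
- Quantitative outcomes: school and school-by-time as fixed effects beside group and time.
- Categorical items: Mantel-Haenszel tests or logistic models stratified by school, in place of the pooled Chi-square.
- Reporting: number of children per arm within each school.

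Section 2.5.2 should also say whether the similar number of controls applies to each school.

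**Cost.** A sentence or two and no new data. With S schools and three measurement times, the terms use S − 1 and 2(S − 1) degrees of freedom, so 1 and 2 for two schools. The Discussion says implementation is still to come, so the change can be made before any outcome is seen.

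**Limit.** A school term cannot separate the intervention from the year 5 versus year 6 difference. That difference is tied to arm in every school, and the Discussion already admits it.

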## 4. Conclusions

The treatment of CD extends beyond dietary measures. Thus, it is now acknowledged that the psychological and social aspects of the disease are equally important. Ensuring the social inclusion of individuals with CD in society is crucial. Therefore, Zeliakide aims to make a societal impact by targeting a significant group: schoolchildren. It is important to note that this protocol has been carefully designed. It is based on well predefined competences and learning outcomes, which are developed through a collaborative-active methodology and are assessed precisely using a specific evaluation tool.

It is anticipated that Zeliakide will be seamlessly integrated into the school curriculum, enhance STEAM competence among children, improve their understanding of balanced and gluten-free diets, and increase knowledge about CD. Additionally, it is expected to foster positive attitude changes towards this topic.

## Figures and Tables

**Figure 1 nutrients-16-00338-f001:**
[figure not shown]
The overview of the Zeliakide intervention study flow. “*Data collection” means the point in time at which data are to be collected.

